## Abstract

**Introduction::**

Repetitive peripheral magnetic stimulation (rPMS) therapy is an innovative and minimally invasive neurorehabilitative technique and has been shown to facilitate neural plasticity. However, there is at present no research that clarifies the dose–response of rPMS therapy on the recovery of upper limb hemiparesis after stroke. This trial aims to clarify the dose–response of rPMS therapy combined with intensive occupational therapy (OT) for chronic stroke patients with moderate to severe upper limb hemiparesis.

**Methods and analysis::**

This multicenter, prospective, assessor-blinded, randomized controlled study with 3 parallel groups will be conducted from January 20, 2020 to September 30, 2022. Fifty patients will be randomly assigned in a ratio of 1:2:2 to the control group, the group receiving daily 2400 pulses of rPMS, or the group receiving daily 4800 pulses of rPMS, respectively. From the day after admission (Day 1), rPMS therapy and intensive OT will be initiated. The primary outcome is the change in the motor function of the affected upper extremity (Fugl-Meyer Assessment) between the time of admission (Day 0) and the day after 2 weeks of treatment (Day 14). Secondary outcomes will include the changes in spasticity, active range of motion, motor evoked potential, and activity of daily living.

**Ethics and dissemination::**

The study was approved by the Jikei University Certified Review Board for all institutions (reference number: JKI19–020). Results of the primary and secondary outcomes will be published in a peer-reviewed journal and presented at international congresses. The results will also be disseminated to patients.

**Trial registration number::**

jRCTs032190191.

## Introduction

1

Stroke is a major global health care problem, and rehabilitation is a major component of clinical management. Among post-stroke sequelae, hand and arm impairment often persists and has a particularly strong impact on a person's activities of daily living (ADL) and quality of life (QOL).^[1]^ The primary goal of stroke rehabilitation is to achieve higher levels of motor function recovery of the affected upper limb, leading to better ADL and QOL.

Recent advances in clinical neurophysiology have led to the development of novel neurorehabilitative techniques for facilitating neuroplasticity and recovery of affected upper limb motor function. Neuromuscular electrical stimulation (NMES) has been developed and validated for improving both the motor function of the affected upper limb and ADL in stroke patients.^[2,3]^ However, NMES has some adverse effects, including pain, dermatitis, and skin burns. Furthermore, the depth of stimulation produced by NMES is very shallow, which does not result in sufficient stimulation of the deep muscles, such as the supraspinatus muscle. In contrast, the beneficial effect of repetitive transcranial magnetic stimulation (rTMS) therapy in patients with post-stroke upper limb hemiparesis has been previously reported.^[4,5]^ However, the beneficial effect of rTMS has only been demonstrated for stroke patients with mild hemiparesis. In addition, the clinical application of rTMS is limited to patients without a history of epilepsy. There is also a possibility that rTMS might lead to the development of epilepsy.

Because of these limitations, this study focuses on the use of repetitive peripheral magnetic stimulation (rPMS) therapy, which is a relatively safe and minimally invasive neurorehabilitative technique. rPMS therapy involves generating a magnetic field in the vertical direction by passing an electric current through a magnetic coil and selectively stimulating a nerve or muscle. The principle behind rPMS is similar to that of NMES; however, rPMS can penetrate the deeper muscle layers and is nearly painless, with virtually no side effects. The repetitive contraction–relaxation cycles produced by rPMS have been shown to both enhance proprioceptive input from the affected extremity, and to increase neuroplasticity.^[6–8]^ Several studies have reported the clinical utility of rPMS therapy in acquired brain injury patients with dysphagia,^[9]^ gait disturbance^[10]^ leg paralysis after stroke,^[11]^ and constipation.^[12]^

Two clinical trials evaluating the effect of rPMS on upper limb hemiparesis have previously been conducted in stroke patients. In the randomized controlled trial (RCT) conducted by Krewer et al, rPMS therapy for acquired brain injury patients with upper limb paralysis had a significantly greater effect on spasticity compared with the sham stimulation group; however, there was no significant effect of rPMS on the motor function of the affected upper limb.^[13]^ The rehabilitation treatment in this study involved passive range of motion (ROM) movements and stretching, and did not include the active training required to facilitate voluntary movements of the hand and arm. We believe that a protocol of rPMS combined with intensive occupational therapy (OT) will provide a therapeutic effect in the improvement of upper limb function. Although a previous case–control study reporting the usefulness of rPMS therapy for patients with subacute stroke^[14]^ has been conducted; there have been no randomized controlled trials that have reported the therapeutic effects of rPMS therapy in chronic stroke patients.

In addition, there is no established protocol that exists for rPMS therapy, and the most effective stimulation count of rPMS per day for functional recovery from stroke is still unknown. With regard to the stimulation frequency, previous neurophysiological and clinical studies have shown that 20 to 30 Hz of rPMS therapy is effective.^[9–10,14–17]^ On the contrary, there are various reports on the total number of rPMS stimuli per day to produce a treatment effect, ranging from 1200 to 16,000.^[9–13]^ In a case–control study focusing on upper limb paralysis, the usefulness of rPMS therapy with a daily total stimulus delivery of 5000 was reported.^[14]^ However, there has been no data reported regarding the dose–response of rPMS therapy.

Therefore, we decided to examine the dose–response of daily total stimulus delivery in rPMS therapy in the treatment of upper limb paralysis secondary to stroke. The purpose of this RCT is to clarify this dose–response when combined with intensive OT in chronic stroke patients with moderate to severe upper limb hemiparesis, comparing three parallel groups. In addition, we aimed to assess the safety of rPMS therapy by comparing the incident rate of adverse events (AE) among groups.

## Methods and analysis

2

### Trial design

2.1

This study is a multicenter, prospective, assessor-blinded, dose–response RCT study with 3 parallel groups. It will be conducted from January 20, 2020 to September 30, 2022. This trial aims to clarify the dose–response of rPMS therapy when combined with intensive OT in chronic stroke patients with moderate to severe upper limb hemiparesis. Two hospitals (the Jikei University Hospital and the Jikei University Daisan Hospital) have been registered as study sites.

### Patient and public involvement

2.2

Neither the patients, nor the public were directly involved in the study design, patient recruitment, and conduct of the study. The obtained results will contribute to better clinical outcomes for stroke patients with upper limb hemiparesis.

### Sample selection

2.3

Inclusion criteria are:

Stroke patients with upper limb hemiparesis between the age of 18 and 80 years;More than or equal to 3 months passing since the occurrence of stroke;Patients with a Brunnstrom Stage of 3 to 4 for the upper limb;Patients with a generally stable condition;Patients with a lack of cognitive impairment, and a good understanding of the study plan;Patients who are able to give written informed consent of their own free will;Patients of female or male sex;Patients who are able to adhere to the study protocol, including hospitalization and outpatient visits; andPatients who have previously been treated with botulinum toxin (BTX) therapy for upper limb paresis.

In this study, we only included patients who had received BTX therapy for their affected upper limb, as this method has been validated for reducing spasticity.^[18]^ In a previous RCT, rPMS therapy was shown to improve spasticity,^[13]^ thus indicating that administration of rPMS may be linked to the improvement of motor function and the reduction of spasticity. Although it might be desirable to include patients without the experience of BTX therapy, it should be considered that recruitment of these patients is difficult, as almost all patients with severe upper limb hemiparesis, who have had spasticity in their affected limb, have been treated with BTX. Based on this, and to ensure the treatment procedure for spasticity is uniform, we decided to recruit stroke patients who have previously received BTX therapy.

Exclusion criteria are:

Patients with a self-contained medical implant (pacemaker, cochlear implant, and so on);Patients with severe heart disease;Patients with metal implants near the rPMS stimulation site;Patients with deep-vein thrombosis near the rPMS stimulation site;Patients with infection (such as acute cellulitis, and so on) near the rPMS stimulation site;Patients who are, or who may be, pregnant;Patients who have unstable diseases that should be immediately treated (such as acute heart failure, acute kidney injury, severe diabetes, infection, and so on);Patients who have received BTX therapy within 2 weeks of admission, as the drug efficacy of BTX is known to gradually develop up to 2 weeks after the injection^[19]^; andPatients who are otherwise considered ineligible for the study according to the researchers.

### Study procedure

2.4

Eligible patients who provide written informed consent will be randomly assigned at a ratio of 1:2:2 to the control group, the group receiving 2400 daily pulses of rPMS (2400 pulses group), or the group receiving 4800 daily pulses of rPMS (4800 pulses group), respectively. Patients will be randomly assigned using a computer-generated list of random numbers using blocked randomization, and stratified by the Fugl Meyer Assessment (FMA) (<20 or ≥20) and age (<65 or ≥65 years’ old). The study researcher will report to the allocator by phone, and the assignment will then be reported to the investigator. The block sizes will not be disclosed to ensure allocation concealment. rPMS therapy and intensive OT will be initiated from the day after admission (Day 1). The evaluation will be conducted on Day 14, after 2 weeks of therapy. After the evaluation, the therapy will be repeated for another 2 weeks (Day 15–28). For the control group, 4800 pulses of rPMS therapy will be performed for relief measures after the evaluation (Day 14). Another evaluation will be conducted 2 weeks after therapy (Day 28). Patients will be discharged on Day 28, after a total of 4 weeks of admission. In addition, the immediate effect of rPMS therapy will be assessed at the time of admission and the first session of rPMS therapy. We will check the long-term effect and safety of the rPMS therapy four weeks after discharge. The study flow chart is shown in Figure 1.

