### Study interventions

2.5

Our study will consist of 2 interventions: rPMS therapy and intensive OT. rPMS therapy will be applied using the Mag Pro R30 stimulator with a 140 mm parabolic coil (Magventure, Denmark). A stimulation coil will be percutaneously placed on the target muscles (Fig. 2). Each train of rPMS stimuli will be applied at 20 Hz for 3 seconds followed by a 27 second rest interval. Eighty such trains of rPMS stimuli will be applied as the daily 4800 pulses of rPMS therapy, and 40 such trains of rPMS stimuli will be applied as the daily 2400 pulses of rPMS, in the respective treatment groups. As the previously mentioned case–control study has shown the usefulness of 4800 pulses of rPMS therapy in the recovery of upper limb motor function in patients with subacute stroke,^[12]^ we decided to clarify the response to this 4800 pulses dose, to half of this dose (2400 daily stimuli of rPMS), and to no treatment. The intensity of rPMS will be individually set to 10% above the minimal level that evoked a joint movement when the patient was at rest.^[10,13]^ The participating physiatrists will select the rPMS stimulation site. In this study, it is required that more than half of rPMS stimulation are performed on the proximal muscles of the upper limb, such as the deltoid, triceps brachii, and supraspinatus. More than 1200 pulses of rPMS in a single stimulation site will be prohibited. The dose will be decreased or the rPMS will be discontinued if the patient requests, or if side effects of rPMS are observed. Once any side effects have improved, the investigator will be allowed to discontinue or resume treatment with modifications, according to the protocol.

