### Sample size estimation

2.10

The target sample size for this randomized trial is 50. This number is based on the results of a previous case–control study in subacute stroke by Yang et al, which compared the improvement of FMA changes between patients who received both rPMS therapy in the shoulder muscles and rehabilitation therapy (treatment group), and the patients who received both NMES therapy and rehabilitation (control group). This study revealed that the FMA score in the rPMS and control groups improved by 11.47 ± 2.72 and 5.40 ± 1.80 (mean ± standard deviation), respectively.^[14]^ Occupational therapy alone has been shown to improve FMA scores by 3.4 in the chronic phase of stroke.^[25]^ Based on these reports, we predicted that a therapeutic effect of the intervention for chronic stroke may occur at a 65% of that for subacute stroke. In addition, we predicted that the therapeutic effect in the group receiving 2400 pulses of rPMS will occur at 50% of those receiving 4800 rPMS in therapy. The estimated changes in the FMA scores of the control group, 2400 pulses group, and 4800 pulses group are therefore 3.4, 5.4, and 7.4, respectively, and the assumed standard deviation is 3. A sample size of 8 patients in the control group, 16 patients in the 2400 pulses group, and 16 in the 4800 pulses group will provide an 80% power to detect differences of the change in FMA among the groups, using the maximum contrast method with contrast coefficients (−1, 0, 1), (−1, −1, 2), (−2, 1, 1) at a 5% level of significance (2-sided). A dropout rate of 20% is allowed. A total sample size of 50 patients is hence required for the trial.

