### Statistical analysis

2.11

The analyses of the primary and secondary efficacy outcomes will be performed using the Full Analysis Set. Safety analysis will be conducted in the safety analysis population. For baseline characteristics, summary statistics will comprise frequencies and proportions for categorical variables, and means and SDs for continuous variables. The patient characteristics will be compared using Pearson *χ*^2^ test or Fisher exact test for categorical variables, and 1-way analysis of variance (ANOVA) for continuous variables.

For the primary analysis, to evaluate the responsiveness of FMA change to the daily total stimulus count of rPMS in chronic stroke patients with upper limb paralysis, the maximum contrast method will be performed with contrast coefficients (−1, 0, 1), (−1, −1, 2), and (−2, 1, 1). A change in the FMA score between Day 0 and Day 14, with the corresponding 95% confidence interval (CI), will be estimated for each group.

For the secondary analysis, Pearson *χ*^2^ test will be performed for categorical variables, and 1-way ANOVA for continuous variables. The significance level of the 2-sided hypothesis test is 5%, and the CI is a 2-sided 95% CI.

For the safety analysis, the frequencies of AEs will be compared using Pearson *χ*^2^ test or Fisher exact test, as appropriate.

All comparisons have been planned, and all *P* values will be 2-sided. *P* values < .05 will be considered statistically significant. All statistical analyses will be performed using SAS software, V.9.4 (SAS Institute, Cary, NC). The plan for statistical analysis was developed by the chief investigator and statisticians, and will be finalized before the database lock.

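### Two hospitals, strata of FMA and age only, and no hospital term in the stated primary test: a cheap adjustment would protect precision with only 10 controls

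*Protocol article*

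**What the plan says.** All references are to the protocol article.

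- Section 2.1 (Trial design): "Two hospitals (the Jikei University Hospital and the Jikei University Daisan Hospital) have been registered as study sites".
- Section 2.4 (Study procedure): patients are "randomly assigned at a ratio of 1:2:2" in blocks, "stratified by the Fugl Meyer Assessment (FMA"), cut at 20, and by age, cut at 65 years. Hospital is not a stratum.
- Section 2.5 (Study interventions): "The participating physiatrists will select the rPMS stimulation site". The same section describes therapist-led sessions adapted to each patient, plus a self-training programme written by the therapists. Every arm receives this therapy.
- Section 2.10 (Sample size estimation): 8, 16 and 16 evaluable patients, assumed FMA changes of 3.4, 5.4 and 7.4, SD 3, and 20% dropout. "A total sample size of 50 patients is hence required for the trial".
- Section 2.11 (Statistical analysis): for FMA change from Day 0 to Day 14, "the maximum contrast method will be performed with contrast coefficients" (−1, 0, 1), (−1, −1, 2) and (−2, 1, 1). No hospital term is named. The analysis plan is to be finalised before database lock.

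The Discussion names the small number of institutions as a limitation but sets no measure against it.

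**The concern.** Part of what a patient receives depends on local staff. Therapists tailor the occupational therapy in all three arms, and physiatrists choose where to stimulate in the two rPMS arms. Mean FMA change may therefore differ between the hospitals for reasons unrelated to dose.

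Nothing in the stated design or test deals with such a difference. Part of it can fall unevenly between arms by chance, and the rest enters the error term. The control arm is the smallest, and it carries a non-zero coefficient in all three contrasts (−1, −1, −2), so an imbalance there touches every one of them. At stake are precision and the credibility of the one randomisation actually drawn, not the long-run error rate.

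**Working it through.** **Inputs from the article:** 1:2:2 allocation, 50 randomised, 8/16/16 evaluable, means 3.4/5.4/7.4, SD 3, two-sided 5%, the three contrasts.

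**Assumptions, because the article gives no figure:** hospital shares of 50:50 (70:30 as a variant), and a hospital difference δ in mean FMA change of 0 to 3 points.

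**1. The plan's own sample size.** Each contrast has standard error SD × √Σ(c²/n):

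- (−1, 0, 1): √(1/8 + 1/16) = 0.433; 4 / (3 × 0.433) = 3.08
- (−1, −1, 2): √(1/8 + 1/16 + 4/16) = 0.661; 6 / (3 × 0.661) = 3.02
- (−2, 1, 1): √(4/8 + 1/16 + 1/16) = 0.791; 6 / (3 × 0.791) = 2.53

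The multiplicity-adjusted two-sided critical value (multivariate t, 40 − 3 = 37 df) is about 2.30. Simulated power is 83.6% at 8/16/16 and 77.8% at 7/14/14, so 8/16/16 is the smallest 1:2:2 set that reaches 80%. Then 40 / (1 − 0.20) = 50, and 50 / 5 = 10 controls. The stated size reproduces.

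**2. Chance imbalance by hospital.** Let X ~ Bin(10, p) be one hospital's patients among the controls and Y ~ Bin(20, p) those in the 4800 arm.

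| Recruitment | P(\|X/10 − Y/20\| ≥ 0.20) | P(≥ 0.30) |
|---|---|---|
| 50:50 | 0.37 | 0.16 |
| 70:30 | 0.33 | 0.12 |

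Against all 40 rPMS patients, with hospital totals fixed (hypergeometric), the 50:50 figures are 0.29 and 0.07.

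**3. What an imbalance does to the estimate.** The shift is the imbalance times δ. For 30 points and δ = 2 it is 0.30 × 2 = 0.6 FMA points, or 0.6 / 4 = 15% of the planned 4800-minus-control difference. For δ = 1 it is 0.3, and for δ = 3 it is 0.9.

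**4. Power at 8/16/16, 50:50, hospital difference added to SD 3** (simulation, hospital allocated at random across arms):

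| δ (FMA points) | As stated, no hospital term | With hospital term |
|---|---|---|
| 0 | about 83% | about 82% |
| 1 | 82–83% | 82–83% |
| 2 | 79–80% | 82–83% |
| 3 | 74–75% | 82–83% |

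With all arm means equal, the rejection rate is about 5% in every setting, with or without the term.

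**5. The other reading of SD 3.** A 50:50 hospital difference adds δ²/4 to the variance. Step 4 therefore implies a total SD of √(9 + 1) = 3.16 at δ = 2 and √(9 + 2.25) = 3.35 at δ = 3. If SD 3 already includes hospital variation, unadjusted power stays at about 82–84% for all δ, and the term raises it to about 86–87% at δ = 2 and about 91% at δ = 3.

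**6. One unlucky draw, as an illustration.** Suppose 6 of 8 controls (75%) but 7 of 16 in each rPMS arm (44%) come from the better hospital, a gap of 31 points. Unadjusted power is then about 67% at δ = 2 and 55% at δ = 3, against about 82% with the term. With a gap of that size, the type I error conditional on it is about 6% and 7%.

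**The case against.** The strongest objection is that a covariate in the primary model is analysis-plan material. That plan is not shown, an article condenses, and section 2.11 does not exclude adjustment. This stands in part. If the plan already contains the term, the sponsor need only confirm it. But the article does state the primary test, its exact contrasts and the power calculation built on them, and no hospital term appears, so a concrete improvement to the stated test is a fair point.

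A second objection is that the gain rests on two undocumented inputs, the hospital shares and the hospital difference. That stands, and it limits the priority. The hospitals belong to one university, and device, frequency, pulse counts and therapy minutes are standardised, so the difference may be small. The shortfall below 80% also disappears if SD 3 is read as the total SD. The term still gains precision on that reading.

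A reader might infer more than the documents support:

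- *That physiatrists also choose intensity.* Section 2.5 sets it by a rule relative to the level that produces joint movement. Site choice is bounded too, and it cannot act in controls before Day 14, since they receive no rPMS until then.
- *That each hospital's own assessors score the FMA.* Section 2.4 says only that the outcome assessors are blinded.
- *That imbalance is likely.* 37% and 16% are appreciable, not likely.
- *That the test is invalid or the randomisation defective.* Average type I error is about 5%. A third two-level stratum would make 2 × 2 × 2 = 8 strata for 50 patients with a smallest 1:2:2 block of 5, leaving many blocks incomplete.

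**Conclusion.** The point holds as an efficiency and robustness improvement, not as an error. The stated primary test makes no use of hospital in a two-hospital trial where therapy is tailored by staff and the control arm has 10 patients (8 evaluable).

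If the hospitals differ by 1 FMA point or less, the effect is negligible. If they differ by 2 to 3 points on top of SD 3, a hospital term recovers roughly 3 to 8 points of power and removes a chance shift of the order of 0.6 to 0.9 FMA points in an imbalanced draw. These sizes depend on the assumed 50:50 recruitment and on the assumed hospital difference, neither of which the article gives. Priority is low to moderate.

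**What to change.** Keep the randomisation and the sample size as they are. Before database lock, prespecify that the three contrasts are taken from a linear model for FMA change with arm (three levels) and hospital (two levels, fixed effect), with the multiplicity-adjusted critical value based on that model. Report mean FMA change by hospital and arm descriptively; with about 8 evaluable controls, the by-hospital figures cannot bear a test.

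The cost is one sentence in the analysis plan, one residual degree of freedom (37 to 36 at 40 evaluable patients), and about 1 point of power if the hospitals do not differ. Fixing the term in advance also avoids a post hoc decision if an imbalance shows up in the data.
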